### Safety and adverse events

Since the intervention, a novel design house is no health or safety risk which could expose participants to harm neither a data safety monitoring board (DSMB) has been appointed nor is an interim analysis planned. It is not reasonable to anticipate that novel design houses which have been carefully planned with regard to safety features will lead to an increase in adverse events.

Study households are visited weekly by research assistants, and structural problems such as tears in the shade net used for screening, solar electricity supply, or water harvesting are addressed and repaired within days. In the unlikely case that the study team is alerted of a safety issue, the problem will be addressed immediately by our standby construction/repair team in charge of building maintenance.

### Auditing

No audits are planned.

### Study endpoints

#### Primary endpoints

Incidence of malaria will be calculated in children under 13 years participating in the study for 3 years, using the number of detected cases as the numerator and the period contributed by each child residing in the study area as the denominator. These data will be analysed and used to determine the relative risk of malaria among children living in the novel design houses compared with those living in traditional sub-Saharan African homes.

#### Secondary endpoints

Incidence of respiratory tract infections and diarrhoea diseases will be calculated, and relative risks determined among children living in the novel design houses compared with those living in traditional African homes.

##### *P. falciparum* prevalence

The prevalence of malaria parasitaemia among children living in novel design houses and traditional homes will be compared in annual malaria surveys. Finger prick blood specimens will be collected from all children participating in the study for *P. falciparum* rapid diagnostic test and dried blood spots for qPCR.

##### Difference in growth parameters

Weight, height, body mass index (BMI), and mid-upper arm circumference of all children participating in the study will be recorded at baseline, annually, and at the end of the study. The mean changes in growth parameters will be compared among children living in intervention and control houses.

##### Difference in disease severity

Differences in disease severity between children residing in novel design houses and traditional homes will be analysed by comparing hospitalization rates.

##### Microbiology

Differences in the frequency of pathogens detected in symptomatic and healthy children will be used to calculate attributable fractions of pathogens and compared between intervention and control houses. Pathogens detected by air sampling will be compared between intervention and control houses.

##### Mean number of malaria vectors/light trap/night

The number and type of mosquitoes from novel design houses and traditional homes will be determined at various time points throughout the study period. This will be used to assess the differences and similarities in mosquito densities between novel design houses and traditional homes as a proxy for measuring exposure to malaria transmission.

##### Environmental measurements

Indoor climate and other relevant environmental metrics will be measured for 3 years using data loggers. This will be used to compare indoor temperature, humidity, carbon dioxide, PM_2.5_ particle pollution, and door opening and closing in both study arms.

##### Acceptability of interventions

The acceptance of novel design houses will be assessed using qualitative and quantitative research methods. Interviews will be conducted 6 months after moving into the houses and after 1 to 2 years.

##### Bednet use

Household heads of traditional and novel design houses will be interviewed annually to estimate the use of ITNs.

##### Durability

Yearly inspections of all study houses will be conducted to assess durability and modifications of the various components of the building structure.

##### Economics

A comparison of construction costs and cost benefits for intervention and control houses will be conducted.

##### Aerosol dispersion

The risk of becoming infected with SARS CoV-2 (COVID-19) between the intervention houses and the control houses via aerosols from another occupant of the same household, will be compared.

### Sample size calculations

Our sample size estimates are based on malaria incidence in Korogwe, Tanzania, observed during the RTS,S cohort phase 3 trial [26]. Malaria epidemiology in Tanzania is quickly changing, and the main burden of disease has moved from young children aged 5–17 months to older children and adolescents. Assuming malaria episodes of 10/100 children/year in the control and a 30% reduction from 10 to 7 malaria episodes/100 children/year, a coefficient of variation (CV) of the outcome of 0.25, as recommended by Hayes and Moulton 2009 [27], detecting the difference in incidence rates with 80% power and testing at 5% significance level, we would need 105 clusters (households) with three child/years of observations per household per arm. To allow for loss to follow-up, we plan to recruit 110 households to the intervention arm. Since analysis requires adjustment for clustering by village and household [28], power simulations were performed using a random effects model to assess what ratio of traditional to novel-design households provides adequate power. For every intervention house, we will recruit four control houses, which will provide at least 80% power at the 5% level of significance to detect a 30% risk reduction. Since ICCs that accommodate village and household level clustering are rarely reported, we compensated for clustering from both levels by choosing a conservatively high ICC of 0.6. Because malaria is generally rarer than either respiratory diseases or diarrhoeal diseases in the study population, the sample size should suffice to measure a 30% reduction in all diseases under investigation at a 5% level of significance and 80% power. The sample size was performed in Stata 15 using the following basic command: clustersampsi, samplesize rates r1(.1) r2(.07) m(10) cluster cv(0.25) alpha(0.05) beta(0.8) base correl (0.6). The simulation results are shown in Fig. 4 below. Simulations were performed in Stata, and each scenario was simulated 5000 times and the empirical power was obtained. We considered 20, 40, 80, and 110 households in the intervention.

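### The stated need for 105 households per arm at three child-years each does not follow from the stated inputs (about 503 are needed); the command behind it uses m(10) and a 0.6 that the text calls an ICC

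*Protocol article*

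**What the plan says.** All of this is in the protocol article, under Sample size calculations.

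- Effect: "Assuming malaria episodes of 10/100 children/year in the control and a 30% reduction from 10 to 7 malaria episodes/100 children/year".
- Clustering: "a coefficient of variation (CV) of the outcome of 0.25".
- Error rates: "with 80% power and testing at 5% significance level".
- Result: "we would need 105 clusters (households) with three child/years of observations per household per arm".
- Allowance: "To allow for loss to follow-up, we plan to recruit 110 households to the intervention arm".
- Command (its closing bracket omitted here): "clustersampsi, samplesize rates r1(.1) r2(.07) m(10) cluster cv(0.25) alpha(0.05) beta(0.8) base correl (0.6".
- The 0.6: the text says that clustering by village and household was covered by "choosing a conservatively high ICC of 0.6".

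The same section then says that separate random-effects simulations support four control houses per novel house with at least 80% power. Their results are in Fig. 4.

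**The concern.** Three things in one paragraph do not agree. The number of households does not follow from the rates, CV, power and person-time given in the same sentence. The person-time in the sentence (3) is not the value in the command (10). The 0.6 is described as a safeguard that enlarges the trial, but it is entered under an option whose name points to a correlation with a baseline measurement, which would shrink it.

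This is the published justification for the primary endpoint. The 110 novel houses are derived from the 105, and the step between them is presented as the allowance for loss. A reader cannot tell from the paragraph how much power the trial has, or how much loss it can absorb.

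**Working it through.** **Inputs.** λ0 = 0.10, λ1 = 0.07, CV k = 0.25, 80% power and 5% significance, all from Sample size calculations. Sidedness is not stated; two-sided is assumed, so (1.960 + 0.842)² = 7.849. Child-years per household, y, has three candidates: 3 (text), 10 (command), and 9 from the Abstract (1650 children / 550 households = 3 children, followed for 3 years).

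**1. The plan's figure.** The usual unmatched formula for rates is

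c = 1 + 7.849 × [(λ0 + λ1)/y + k²(λ0² + λ1²)] / (λ0 − λ1)²

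with λ0 + λ1 = 0.17, λ0² + λ1² = 0.0149 and (λ0 − λ1)² = 0.0009.

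| y | c per arm | no clustering: 7.849 × (0.17/y)/0.0009 | c with variance × 0.64 |
|---|---|---|---|
| 3 | 503.3 | 494.2 | 322.5 |
| 9 | 173.9 | 164.7 | 111.6 |
| 10 | 157.4 (158 rounded up) | 148.3 | 101.1 (102 rounded up) |

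At y = 3 no variant tried comes near 105: one-sided 397, log scale 507, square-root scale 490, binomial variance 460, and 281 novel houses at 1:4. Without the last column's reduction, 105 per arm would need about 15.5 child-years per household.

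**2. Power at 105 per arm, y = 3.** Per-household variances are 0.10/3 + 0.0625 × 0.01 = 0.03396 and 0.07/3 + 0.0625 × 0.0049 = 0.02364. SE = √(0.05760/105) = 0.0234, and 0.03/0.0234 = 1.28. Power = Φ(1.28 − 1.96), about 25%.

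**3. Where 105 may come from.** If `base correl (0.6)` is a correlation with a baseline value, the variance is multiplied by 1 − 0.6² = 0.64. With m(10) this gives about 102, within 3% of 105. The protocol article does not define the option; this meaning is inferred from its name.

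**4. What an ICC of 0.6 would do.** The unclustered total is 7.849 × 0.17/0.0009 = 1482.6 child-years per arm. With design effect 1 + (m − 1) × 0.6, the number of households is 1482.6 × 2.2/3 = 1087 at m = 3 and 1482.6 × 6.4/10 = 949 at m = 10. An ICC raises the requirement; the figure of 105 lies below the no-clustering column.

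**5. The design being run, 110:440, household CV 0.25, before village clustering.**

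- *Rate difference, y = 9.* Variances are 0.01174 (control) and 0.00808 (novel). SE = √(0.00808/110 + 0.01174/440) = 0.01001, and 0.03/0.01001 = 3.00. Power is about 85%. At 1:4 the formula needs 1 + 7.849 × (0.00808 + 0.01174/4)/0.0009, about 97 novel houses.
- *Log rate ratio, y = 9.* SE = √[(1/0.63 + 0.0625)/110 + (1/0.90 + 0.0625)/440] = 0.1329, and 0.3567/0.1329 = 2.68. Power is about 77%. At 1:4 the need is 7.849 × [1.6498 + 1.1736/4]/0.3567², about 120 novel houses.
- *y = 8.* The same steps give about 81% (rate difference) and 72% (log ratio).

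**The case against.** The strongest reply is that 105 is not arbitrary: the full printed command, with its last option read as a baseline correlation, gives about 102. That stands, and it means 158 is not what the whole command implies. It does not rescue the sentence. The text states three child-years and describes the 0.6 as working in the opposite direction. The Analytical plan lists year, age, gender, ethnicity and rainfall but no baseline incidence term, and surveillance began in January 2022, after the houses had been handed over. The survey at the start of the study measures parasite prevalence, not incidence.

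It can also be said that 105:105 at three child-years is not the trial being run, and that 110:440 rests on separate simulations. Both are true. The 25% therefore measures how wrong the sentence is; it is not the trial's power.

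Two stronger readings are tempting. A reader might convert 110:440 by 2/(1/110 + 1/440) = 176 per arm, set that against 174, and infer that nothing is left for loss. The shortcut assumes equal variances in the two arms, whereas the formula behind 174 does not. On that formula 110:440 is worth 0.01982/0.01001², about 198 per arm, and 97 novel houses suffice. On the log scale it is worth about 160 per arm against 174 needed. Whether there is a margin depends on the scale. A reader might also infer that the claim of at least 80% power is false. The results in Fig. 4 are not shown, so the documents at hand neither support nor refute that.

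**Conclusion.** The paragraph is wrong as written and has to be corrected. At three child-years the stated inputs need about 503 households per arm, nearly five times the stated 105. The text and command disagree on person-time (3 against 10), and the planned cohort gives a third value, about 9. The 0.6 is called a conservative ICC but appears to have lowered the requirement at m(10) from about 158 to about 102.

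The trial itself is less affected than the sentence. At nine child-years the 110:440 design has power from about 77% to 85%. Nine is an upper value for three children over three years, because the Analytical plan removes travel, nights away and four weeks after each malaria treatment, and the section on bias also censors children who do not regularly sleep upstairs. At eight child-years power is about 72% to 81%.

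These figures assume two-sided testing, household CV 0.25, equal person-time per household and no village-level variation. The direction in which the 0.6 acted rests on the name of the option.

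**What to change.** Rewrite the paragraph; keep the houses and households.

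1. Replace the three child-years with the person-time expected per household: about nine, less the time to be censored. Use the same value in the command.
2. Remove the 0.6 baseline-correlation term, or name the baseline measurement and the analysis that would use it. In either case stop describing it as a conservative ICC.
3. Restate the requirement and the power for 110:440 on one named scale, without mixing scales. The log rate ratio is closest to the planned mixed Poisson model: about 174 per arm at 1:1 and about 120 novel houses at 1:4 for nine child-years, with power of about 77% at nine and 72% at eight. On the rate-difference scale the corresponding figures are 174, 97, 85% and 81%. State that village clustering is not included, or include it.
4. Derive the loss allowance from that calculation, not from the step from 105 to 110.
5. Give the person-time, CV and test used in the Fig. 4 simulations, so that their power claim can be set beside the formula.

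The cost is one paragraph and a stated margin that may look less favourable.

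### The ICC of 0.6 offered as conservative cover for clustering is not an ICC in the printed calculation, and the 80% power claim is supported only at low household clustering

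*Protocol article*

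**What the plan says.** Everything is in the protocol article, Sample size calculations.

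- **Rates:** "Assuming malaria episodes of 10/100 children/year in the control", with "a 30% reduction from 10 to 7 malaria episodes/100 children/year".
- **Clustering, first statement:** "a coefficient of variation (CV) of the outcome of 0.25".
- **Result for equal arms:** "we would need 105 clusters (households) with three child/years of observations per household per arm".
- **Result for 110:440, from random-effects simulations:** four control houses per intervention house, "which will provide at least 80% power at the 5% level of significance to detect a 30% risk reduction".
- **Clustering, second statement:** for village and household together, "we compensated for clustering from both levels by choosing a conservatively high ICC of 0.6".
- **Other outcomes:** because malaria is the rarer disease, "the sample size should suffice to measure a 30% reduction in all diseases under investigation".
- **Printed command:** rates 0.1 and 0.07, `m(10)`, `cv(0.25)` and `base correl (0.6)`. It contains no ICC option.

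The variance components used in the simulations are not given in the text. Figure 4 is not available here.

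**The concern.** A between-household CV and a household ICC are two ways of writing the same variance. At these rates 0.25 and 0.6 are far apart, so they cannot both describe it. The paragraph tells the reader that power was protected against strong clustering, while the one calculation that can be inspected carries almost none.

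The power statement will be used to interpret a null malaria result. If it rests on weak household clustering but is presented as robust to strong clustering, a null result would be taken as firmer evidence against a 30% reduction than it is. The same statement is then extended to respiratory and diarrhoeal disease without saying what household variation it assumes for them.

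**Working it through.** **Inputs.** Rates 0.10 and 0.07 per child-year, CV k = 0.25, 80% power and 5% significance (two-sided assumed) are from Sample size calculations. The 110 and 440 households are from Study design. Child-years per household (y) take three values: 3 in the text, 10 in the command, and about 9 implied by the Abstract (330 and 1320 children, so three per house, for three years).

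**1. The stated 105 per arm.** The Hayes–Moulton formula for rates is

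c = 1 + (1.960 + 0.842)² × [(0.10 + 0.07)/y + k²(0.10² + 0.07²)] / (0.03)².

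At y = 10: 1 + 7.849 × (0.01700 + 0.00093)/0.0009 = 157.4, so 158. At y = 9 it is 174, and at y = 3 it is 504. None is 105.

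Suppose `base correl (0.6)` multiplies the variance by 1 − 0.6² = 0.64. Then at y = 10, 1 + 0.64 × 156.4 = 101.1, so 102. This is the closest reading found, within 3% of 105. How the option works is an assumption. On this reading 0.6 reduces the sample size. No variant tried with 0.6 as an ICC gave 105.

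**2. CV and ICC on one scale.** In a mixed Poisson model ICC = k²μ/(1 + k²μ).

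- k = 0.25: ICC = 0.006 for a child-year (μ = 0.1) and 0.018 for a child's three-year count (μ = 0.3).
- ICC = 0.6: k = √(1.5/μ), which is 3.87 or 2.24.

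**3. Power for 110:440.** Log scale: Var = 1/(110 × 0.07y) + 1/(440 × 0.10y) + k²(1/110 + 1/440), and power = Φ(0.3567/SE − 1.96). Rate scale: Var = (0.07/y + 0.0049k²)/110 + (0.10/y + 0.01k²)/440, and power = Φ(0.03/SE − 1.96).

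Example, y = 9, k = 0.25, log scale: 1/69.3 + 1/396 + 0.0625 × 0.01136 = 0.01767; SE = 0.1329; power 77%.

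| Household CV | y = 9, log / rate | y = 10, log / rate |
|---|---|---|
| 0.25 | 77% / 85% | 81% / 88% |
| 0.5 | 72% / 81% | 76% / 84% |
| 1.0 | 56% / 65% | 59% / 68% |
| 2.24 | 26% / 30% | 26% / 31% |

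At y = 3 and CV 0.25 power is 35% / 42%. So the stated 80% reproduces at about CV 0.25–0.5 with nine to ten child-years, and not with three.

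**4. If 0.6 were an ICC wholly between households.**

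- Three-year child counts (k = 2.24): 26% log, 30–31% rate.
- k² = 0.6 × 0.9/0.1 = 5.4 (k = 2.32): 29%, rate scale.
- Design effect 1 + (m − 1) × 0.6 with m = 9 or 10 (5.8 or 6.4): about 25% rate, 21% log.
- Simulation with 55 villages of 2 + 8 houses (a simplification): 26–29%.
- Yearly counts (k² = 15): about 15% on the rate scale, 18–19% simulated.
- Design effect 2.2, with three children as the units and y = 9: 54–57%, or 46% on the log scale.
- Three child-years: 13–24% on the rate scale.

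No reading reaches 80%.

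**5. If part of it lies between villages.** The village is the block, so the treatment comparison is made within villages. With clustering mainly between villages (household CV 0.25) the simulations gave 71–76%; a separate set with all of it between villages gave 78–80%. A half-and-half split gave 33–42%.

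**6. Commoner outcomes (log scale, y = 9).** From 0.1 to 0.3 episodes per child-year, power rises from 77% to 99% at CV 0.25 and from 56% to 78% at CV 1.0. With unlimited events only the k² term remains, and 80% power then needs k ≤ 0.3567/(2.802 × √0.01136) = 1.19.

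**The case against.** A reader might infer that the trial has only about 26–31% power. The document does not support that. It says 0.6 covers village and household together, and blocking on village removes much of any village share. Nothing shows that household clustering is really that strong. The figure also depends on the ICC definition: the range is about 13–57% across definitions and child-years.

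A reader might also infer that the simulations behind the 80% used a CV of 0.25. That is visible only for the 105-per-arm step. The simulation inputs are not printed, and 0.6 may simply be a mislabelled correlation, in which case power at an ICC of 0.6 describes a value nobody assumed.

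Finally, a reader might call the sentence on all diseases wrong. At equal CV, or at equal ICC, commoner outcomes do have more power, so its direction is right. It fails only if household variation is larger for those diseases.

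These limits stand, and the low power figures must stay conditional. They do not rescue the statement that 0.6 is conservative: the visible calculation holds no such ICC, and the most plausible role of 0.6 there works in the opposite direction. That allocation is finished does not matter either, because the correction concerns how the result will be read.

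**Conclusion.** The claim that an ICC of 0.6 gave conservative cover for clustering is not supported by the printed calculation. The clustering actually printed is 30 to 100 times weaker on the ICC scale (0.018 to 0.006 against 0.6).

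Power of about 80% for 110:440 is supported at a household CV of about 0.25–0.5 and nine to ten child-years per household. It falls to 56–68% at CV 1.0, and to 35–42% at CV 0.25 if the text's three child-years is taken literally. An ICC of 0.6 would leave about 25–31% on the main definitions if wholly between households, and about 71–80% if mainly between villages.

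These figures assume a two-sided 5% test, a true rate ratio of 0.70 and equal child-years per household. The role given to the baseline-correlation option is an assumption. The sentence on all diseases needs a condition, not removal.

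**What to change.** 1. State what 0.6 is and at which level it acts. Withdraw the claim that it is conservative cover unless the simulations really used it as an ICC.
2. Use one set of clustering parameters and one figure for child-years per household in the text, the command and the simulation, and print the simulation's village and household variance components.
3. Restate power for 110:440, or the detectable reduction, by within-village household CV, for example 0.25, 0.5 and 1.0.
4. Make the extension to respiratory and diarrhoeal disease conditional on their household CV being no larger than that assumed for malaria.

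The cost is rewriting part of one paragraph and rerunning an existing simulation. No households are added. The downside is that the stated power becomes less favourable.

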**Fig. 4 Fig4:**
[figure not shown]
Simulated power calculations showing power by ratios of intervention to control houses, assuming a 30% reduction in all diseases under investigation

### Entomological outcomes

We postulate that the intervention homes will reduce indoor collections of malaria vectors by at least 50%. Based on a recent study using light traps in the Kilombero Valley, Tanzania, the mean number of female *An. gambiae* s.l. per trap in a house was 10.4 (SD = 21.5). Computer simulations based on a negative binomial distribution suggest 89% power at the 5% level of significance to detect a 50% reduction in indoor-entering mosquitoes (i.e. *An. gambiae* s.l.) 110 Star Homes and 440 control houses will be needed. We propose to collect a sample from each house every 7 weeks each year for 3 years.

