**Methods/study design:**

This is a household-randomized, controlled study in 60 villages in Mtwara, Tanzania. A total of 550 households are randomly selected, 110 of which are allocated a novel design house and 440 households continue to reside in traditional houses. A dynamic cohort of about 1650 children under 13 years will be enrolled and followed for 3 years, approximately 330 living in novel design houses and 1320 in traditional rural houses. The primary endpoint is the incidence of malaria; secondary endpoints are incidences of acute respiratory tract infections and diarrhoea diseases detected by passive and active surveillance. Exposure to malaria vectors will be assessed using light traps in all study houses. Structural, economic, and social science studies will assess the durability, cost-effectiveness, and acceptability of the new houses compared with traditional housing. Environmental data will be collected indoors and outdoors in study homes to assess the differences between house typologies.

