### Entomology

Standard CDC light traps will be used to estimate the potential exposure to malaria mosquitoes in the bedrooms of study children in 110 novel design houses and their nearest comparison house from October 2021 to December 2023. The study area will be divided into seven geographically separated clusters, six each with 16 Star homes and 16 control houses and one with 14 Star homes and 14 control houses. Each cluster will further be divided into four sub-clusters, each with eight houses: four Star homes and four nearest neighbours’ control houses. The light traps will be suspended 1 m from the ground at the foot end of a bed where a study child is. Collections will be made from one cluster each week, with a different sub-cluster sampled on four consecutive nights each week, Monday night to Thursday night. At the end of the week, all houses will be sampled in each cluster (i.e. 32 houses). The sequence in which clusters will be visited was randomly determined. The clusters will be visited in the same sequence throughout the study period, so that each cluster will be visited in a 7-week cycle. Malaria vectors collected in the study houses will be counted and compared between the intervention and control houses and then packed in the Eppendorf tubes containing silica gel and submitted to the laboratory, for further analyses. The mosquitoes will be identified by microscopy and the numbers of *An. gambiae* s.l., *An. funestus* s.l., and other species will be recorded. The presence of sporozoites will be identified using an enzyme-linked immunosorbent assay [24], and *An. gambiae* s.l. females, typed by PCR [25].

The abundance and species of domestic flies will be assessed using baited traps installed in the cooking area of selected households, outdoors, and in latrines to assess the difference in fly densities between the two study arms. The traps will be positioned on the kitchen floor, in the corner furthest from the main door. Research assistants will collect the captured flies each evening.

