#### Entomology (malaria transmission)

Differences in malaria transmission experienced in the two groups will be made by comparing the mean number of malaria mosquitoes (as a proxy for transmission) caught indoors in houses between the study arms. Generalized estimating equations will be used to estimate the differences in numbers of indoor-resting mosquitoes, adjusting for repeated measures within houses and possible covariates. We will compare the entomological inoculation rate in both arms. Human behavioural studies will also be carried out to compare when people move indoors and outdoors of the house, since the new housing intervention may change the way individuals use a house, which changes their exposure risk. Observers will record human movement including the age and gender of individuals with their identity anonymized.

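### The 89% entomology power is stated for 440 control houses, but the trapping plan covers 110; the house numbers must be reconciled and the power restated for the design that is run

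*Protocol article*

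**What the plan says.** Three places in the protocol article describe the light-trap work.

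- **Entomological outcomes (sample size).** The target is to "reduce indoor collections of malaria vectors by at least 50" per cent. The control distribution comes from an earlier Tanzanian study in which the mean catch "per trap in a house was 10.4 (SD = 21.5"). The power claim is "Computer simulations based on a negative binomial distribution suggest 89% power at the 5% level of significance", and for this "110 Star Homes and 440 control houses will be needed". The section adds: "We propose to collect a sample from each house every 7 weeks each year for 3 years".
- **Entomology (methods).** Traps are set "in 110 novel design houses and their nearest comparison house from October 2021 to December 2023". Six clusters hold 16 novel and 16 control houses each, and a seventh holds 14 and 14. One cluster is trapped per week, so the cycle takes seven weeks.
- **Abstract, Methods/study design.** "Exposure to malaria vectors will be assessed using light traps in all study houses".

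The Analytical plan compares catches by generalized estimating equations, "adjusting for repeated measures within houses and possible covariates".

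**The concern.** The sample size section treats 440 control houses as a requirement for its power figure. The methods trap a quarter of that number, and the Abstract implies 550 houses in total. These are different studies, and the article does not say which one the 89% describes. A reader of the sample size section or the Abstract would credit the trial with 330 trapped control houses that the field schedule does not visit. A field team would run a different programme depending on which section it followed.

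The period differs too: three years in the sample size section, 27 months in the methods. At stake is the stated precision of the main exposure comparison, a secondary endpoint that the protocol uses as its proxy for malaria transmission.

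**Working it through.** **Houses in the field schedule.** 6 × (16 + 16) + (14 + 14) = 220, which is 110 per arm. At most 32 houses are trapped per week. Visiting 550 houses in a seven-week cycle would need 550 / 7 ≈ 79 per week, so the schedule in the methods cannot cover all study houses.

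**Inputs for power.** Control mean 10.4, SD 21.5, reduction 50% (so 5.2 in novel houses), significance level 5%, all from the sample size section. Assumed here: a two-sided test and the same negative binomial dispersion in both arms.

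Dispersion = (SD² − mean) / mean² = (462.25 − 10.4) / 108.16 = 4.178.

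For one catch per house:

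- Var(log ratio) = (1/5.2 + 4.178)/n₁ + (1/10.4 + 4.178)/n₀
- Power = Φ(ln 2 / SE − 1.96)

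**Reproducing the stated figure, 110 against 440.** Var = 4.370/110 + 4.274/440 = 0.03973 + 0.00971 = 0.04944, so SE = 0.2223. Power = Φ(3.117 − 1.96) = Φ(1.157) = 87.6%. A negative binomial simulation of 4,000 runs gave 89.4% (Wald test) and 87.8% (likelihood ratio test). The stated 89% is thus approximately reproduced. Other readings fit less well: a one-sided test gives 93.0%, and normal approximations give 62.1% (equal SD) or 94.6% (unequal variances).

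**Same basis, 110 against 110.** Var = 4.370/110 + 4.274/110 = 0.07858, so SE = 0.2803. Power = Φ(2.473 − 1.96) = Φ(0.513) = 69.6%. Simulation gave 69.4% (Wald) and 68.4% (likelihood ratio).

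**With repeat catches.** October 2021 to December 2023 is about 117 weeks, and 117.3 / 7 = 16.8, so 16 complete rounds. (Three years would allow 156.5 / 7 = 22.4.) Assume 16 catches in every house and an exchangeable within-house correlation ρ. The variance above is then multiplied by (1 + 15ρ)/16. The protocol gives no value of ρ for trap catches, so a range is shown.

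| ρ | Variance factor | Power, 110 against 110 |
|---|---|---|
| 0.2 | 0.250 | above 99% |
| 0.3 | 0.344 | 98.8% |
| 0.5 | 0.531 | 92.4% |
| 0.6 | 0.625 | 87.9% |
| 0.8 | 0.813 | 78.3% |
| 1.0 | 1.000 | 69.6% |

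Power is 89% or more for ρ up to about 0.58. Using 22 rounds moves that threshold only to about 0.58 as well (0.576 with 16 rounds, 0.583 with 22), so the number of rounds matters little in this range.

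**Could the 89% already include repeats with 440 controls?** With 16 catches per house, 110 against 440 gives 99.0% at ρ = 0.5 and comes down to 89.1% only at ρ = 0.95. One catch per house is the simpler reconstruction, but the simulation settings are not shown.

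**The case against.** The strongest reply is that the contradiction may cost no power. A reader might infer from the one-catch comparison that the planned trapping has only about 70% power, or that shortening three years to 27 months causes the loss. The protocol supports neither. Trapping duration enters neither one-catch figure, and 70% would apply to the planned design only if catches in a house were perfectly correlated. The only correlation the protocol states is the ICC of 0.6 for the clinical outcomes, which it calls conservatively high. Even if that value is borrowed, 110 against 110 gives 88%, one point below the stated figure. This part of the objection stands: the actual power cannot be fixed from the document and may be ample.

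A reader might also fault the end of trapping in December 2023, a year before clinical surveillance ends. Nothing in the protocol requires trapping through 2024, and three years could mean the calendar years 2021 to 2023. It is a mismatch of wording to clear up.

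Nor does the protocol show that the estimating equations mishandle the pairing of neighbouring houses. It allows for covariates, and which ones enter is detail commonly left to an analysis plan that is not shown.

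None of this removes the central conflict. The article ties a power figure to a required number of control houses, and its own methods trap a different number.

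**Conclusion.** The point holds as a contradiction in a stated figure. The sample size section attaches 89% to 110 against 440 houses, the methods trap 110 against 110, and the Abstract says all study houses. On the one-catch calculation that best reproduces the 89%, replacing 440 controls by 110 lowers power to about 70%. For the roughly 16 rounds planned, power for 110 against 110 lies between about 70% and over 99%, and it matches or exceeds the stated 89% only if the within-house correlation is at most about 0.58.

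These figures rest on a two-sided test, equal dispersion in both arms, exchangeable correlation and all 16 catches being obtained. The arithmetic is firm under those assumptions, but the loss of power in the design actually run is undetermined. The matter concerns a secondary endpoint and should be corrected because the figure as written describes a design that the methods do not.

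**What to change.** 1. State one number of control houses to be trapped, and use it in the Abstract, the Entomology methods and the sample size section. The document alone does not settle which number governs.
2. State one trapping period, reconciling three years with October 2021 to December 2023.
3. Rerun the simulation for that design and report the houses per arm, the number of rounds, the assumed within-house correlation with its source or a range, and whether the test is two-sided.

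The cost is wording and one rerun simulation. If the layout with 110 controls is the one kept, no extra trapping is needed to restate the figure. The sponsor should accept that the restated power may be less favourable than 89%.
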